**Fig. 2 Fig2:**
[figure not shown]
OPTIMISTIC patient pathway. Visit 1 and visit 2 can be combined if appropriate and acceptable to participant. Duplicate tests and questionnaires will not be performed

The baseline period constitutes either a combined screening/baseline visit if the genetic diagnosis of DM1 is confirmed or a separate screening visit, in which to obtain a blood sample for DM1 genetic status, followed by a baseline visit, if confirmed. Depending upon the medical and DM symptom history obtained from non-confirmed participants, they may carry out all screening and baseline activities while awaiting the genetic confirmation. This will allow those participants to enrol into the screening phase of the study prior to genetic confirmation. It is of the opinion of the specialists that non-confirmation will occur in very few cases.

Participants will not be blind to allocation, but the study outcome measures listed in the Appendix will be collected by staff who are blind to allocation.

### Study population

#### Number of participants

Participants will be recruited from myotonic dystrophy clinics and neuromuscular centres in the UK, the Netherlands, Germany and France. A total of 296 (male and female) patients will be recruited (see *Inclusion criteria* and *Exclusion criteria*). The figure of 296 allows for drop-outs; 208 are needed to complete the study with regard to our primary outcome (the DM1-Activ scale). This sample size for the primary outcome means that the study is also powered for one of the secondary outcomes, the 6-minute walk test. See *Sample Size Calculation* for more details with regard to participant numbers.

Participants will be randomised to receive a 10-month tailored behavioural change intervention (n = 148) or standard care (n = 148). The flow of participants through the trial is shown in Fig. 3.

**Fig. 3 Fig3:**
[figure not shown]
OPTIMISTIC Study flowchart

For the biomarker study and DNA analysis, whole blood will be collected in a standardised manner from all 296 DM1 participants enrolled in the trial, with 3 × 10 ml whole blood samples collected per patient and sent to a central sample storage facility, the University of Newcastle Biobank. This facility will undertake DNA and serum preparation and send one whole blood sample per participant to Nijmegen University for ribonucleic acid (RNA) preparation.

Samples will be collected at baseline, 10 months (the end of the intervention period) and at 6-month post-intervention (that is, 16 months from baseline). All samples will be obtained, processed and stored as per the Study Operations Manual, which addresses local policies and guidelines.

#### Inclusion criteria

Judgements as to whether a potential participant meets an inclusion criterion are made by the treating clinician unless stated otherwise. Inclusion criteria are as stated below:Able to provide informed consent.Genetically proven DM1, aged 18 years and older, suffering from severe fatigue (CIS-fatigue severity subscale score ≥35) [11]. The genetic diagnosis and level of fatigue will be determined as part of the eligibility screening process.Ability to walk independently (ankle-foot orthoses and canes are accepted).

Carers inclusion criteria involve the ability to give informed consent and to complete study questionnaires.

#### Exclusion criteria

Judgements as to whether a potential participant meets an exclusion criterion are made by the treating clinician unless stated otherwise. Exclusion criteria are as stated below:Neurological or orthopaedic co-morbidity interfering with the interventions or possibly influencing outcomes.Use of psychotropic drugs (except Modafinil, Ritalin and antidepressants where the dosing regimen has been stable for at least 12 months prior to screening). If the doses of Modafinil or Ritalin increase during the 10 months of intervention/non-intervention then the participant will be excluded.Severe depression at screening as per clinical judgement.Participation in another clinical trial of an investigational medicinal product (CTIMP) or other interventional study considered to influence outcomes being evaluated in OPTIMISTIC concurrently or within 30 days prior to screening for entry into this study.Unable to complete study questionnaires.

The exclusion criteria for carers are the inability to give informed consent, complete questionnaires and attend CBT sessions with participants.

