## Background

Myotonic dystrophy type 1 (DM1) is a rare, inherited, progressive disease as well as an autosomal dominant multi-systemic disorder. It is one of the most common adult forms of muscular dystrophy, with a prevalence of approximately 10 per 100,000 people affected [1, 2]. With 733 million people in Europe, we estimate that 75,000 are DM1 patients [3]. Typical symptoms of the disease include progressive muscle weakness and wasting from distal to proximal, ptosis; weakness of facial, jaw and anterior neck muscles; myotonia; daytime sleepiness; fatigue and cataracts. Other symptoms of adult DM1 include cardiac conduction defects, as well as endocrine, gastrointestinal and cognitive dysfunction. DM1 is one of the most variable human diseases, has complex, multi-systemic and progressively worsening clinical manifestations and leads to severe physical impairment, restricted social participation and premature death [4, 5].

There is no pharmaceutical treatment for causal or symptomatic relief of DM1 core symptoms, with the exception of Modafinil for excessive daytime sleepiness and mexiletine for myotonia. Thus, the aim of treatment is to relieve impairments, reduce limitations and optimise participation. Physical activity has been acknowledged as an important factor for health in general. For patients with a slowly progressive neuromuscular disease, such as DM1, there is accumulating evidence for prescribing low-to-moderate-intensity strength and aerobic exercise training, and an active lifestyle [6]. Nevertheless, recent reviews conclude that existing studies are limited in number and quality, and that there is a need for disease-specific, randomised, controlled trials investigating the effect on quality of life [6–8].

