### Rationale for the study

It was demonstrated recently by OPTIMISTIC Partner 1 (see *The OPTIMISTIC Consortium* for list of partners) that severe fatigue, defined as a score equal to or higher than 35 on the subscale fatigue of the Checklist Individual Strength (CIS-fatigue), was reported by around 70 % of patients with DM1 [9]. These severely fatigued patients had more problems with physical and social functioning as well as with their mental and general health than similar patients without severe fatigue. They also had more problems with concentration and planning. As such, experienced fatigue should be clearly distinguished from muscle weakness, which is probably the most common and characteristic symptom of DM1 and also of a lack of initiative (apathy) that is known to occur often in DM1.

In a longitudinal study, we built a model of perpetuating factors for fatigue in patients with DM1 (Fig. 1). It appeared that lack of physical activity, sleep disturbances and pain all contributed to experienced fatigue. In addition, loss of muscle strength and pain contributed to fatigue through a lower level of physical activity. Ultimately, experienced fatigue and physical activity both contributed to the level of societal participation [10]. A lack of initiative (motivation in the model of Fig. 1) further increased fatigue but also had a direct negative effect on societal participation. Thus, theoretically, in order to improve societal participation one should compensate for a reduced initiative, optimise physical activity and alleviate experienced fatigue. To alleviate fatigue one should address the fatigue maintaining factors identified by the model, for example, experience of pain or sleep disorders.

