##### 2. Fatigue and sleepiness (10 min)

Fatigue and Daytime Sleepiness Scale (FDSS)Checklist Individual Strength (CIS) subscale fatigue severity

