### Withdrawal procedures

#### Withdrawal from randomised therapy

Any clinician involved in the usual care of patients may withdraw patients from randomised intervention therapy using his/her clinical judgement. This might occur due to the occurrence of an adverse event and the onset of symptoms that limit tolerability. Participants withdrawn from randomised intervention therapy will remain in the study and will be included in the primary intention-to-treat analysis unless they request that their data are removed. If withdrawal is due to an adverse event it will be logged as such on the Adverse Event Log. All reasons for withdrawal will be noted in the participant’s Case Report Form and medical case notes. The participant and carer will be invited to attend the withdrawal visit. The measurements and activities scheduled at Visit 5 will be performed in the priority set out in the schedule table Appendix incorporating the participants and carers preferences. If a participant is randomised into the study with an immediate family member and either withdraw the other will be able to continue in the study.

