#### Proposed analysis

The primary analyses will be conducted according to the principles of intention to treat (ITT) as outlined on the ICH E9 ‘Statistical Principles for Clinical Trials’.

Continuous variables will be summarised by the number of observations, number of missing values, mean, standard deviation (SD), median, inter-quartile range (IQR) and range. Summaries will be provided at baseline, at each subsequent time point and for the change from baseline by intervention group. Categorical variables will be summarised by the number of observations, number of missing values and number and percentage in each category. Summaries will be provided at baseline and at each subsequent time point.

The primary outcome and most other outcomes are continuous and so linear models will be utilised. The primary outcome of change in DM1-Activ will be analysed using mixed effects (repeated measures) regression models. Models will include fixed effects for intervention group, time point, and their interaction, plus random effects for each subject to account for repeated measures, and will assume a general covariance structure. A binary variable will be added to the regression model to represent the difference between the intervention and standard care. The minimisation variables of severity of DM1 (measured using the MIRS 5-point scale) and caregiver involvement at baseline will also be added to the regression model as fixed effects, as well as stratification by site.

Intervention effect differences will be reported with 95 % confidence intervals (CIs) and *P*-values. Results will also be explored and reported with additional *a priori* adjustment for potential effect modifiers (see list in *Measures used as potential effect modifiers*). Subgroup analyses will be carried out by first testing for a subgroup factor by intervention interaction [16]. If this is significant at the 5 % level, results will be estimated separately by the different subgroups. These analyses will also be repeated for all the secondary outcomes. Appropriate transformations of outcomes will be performed where necessary to satisfy modelling assumptions.

A statistical analysis plan (SAP) will be written prior to datalock and approved by the statistician and CI. Analyses will be carried out using SAS.

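### The rule that excludes participants after a rise in Modafinil or Ritalin dose acts after randomisation, does not say what they are excluded from, and is not reconciled with intention to treat

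*Protocol article*

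**What the plan says.** In the protocol article, *Exclusion criteria* bars psychotropic drugs but admits users of Modafinil, Ritalin or antidepressants whose regimen was stable for at least 12 months before screening. It then adds: "If the doses of Modafinil or Ritalin increase during the 10 months of intervention/non-intervention then the participant will be excluded".

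Three other places bear on this sentence:

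- *Proposed analysis*: "The primary analyses will be conducted according to the principles of intention to treat (ITT"), with reference to ICH E9.
- *Withdrawal from randomised therapy*: "Participants withdrawn from randomised intervention therapy will remain in the study and will be included in the primary intention-to-treat analysis", unless they ask for their data to be removed.
- *Withdrawal of consent to follow-up*: data collection stops when the participant withdraws consent. A drug change is not mentioned.

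*Primary outcome* places the DM1-Activ endpoint at the close of the ten-month period, which is also where the dose rule's window closes.

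**The concern.** The sentence stands among the eligibility criteria, but its trigger can occur only after allocation, and its wording covers both arms. It is therefore a post-randomisation removal rule. Intention to treat compares the groups as randomised; removing people for something that happens later breaks that comparison if the removal is related to outcome and differs by arm.

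The document itself makes both conditions plausible:

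- *Background* says there is no drug treatment for the core symptoms, "with the exception of Modafinil for excessive daytime sleepiness and mexiletine for myotonia", so a rise in Modafinil dose may signal worse sleepiness.
- Sleepiness and fatigue are secondary outcomes (the FDSS and CIS-fatigue).
- *Rationale for the study* links fatigue to the construct behind the primary outcome: "Ultimately, experienced fatigue and physical activity both contributed to the level of societal participation".
- *Study description* says: "Participants will not be blind to allocation". Dose requests and dose reviews can therefore depend on the arm.

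The practical stake is irreversibility. If a site reads the rule as ending follow-up, the month-10 DM1-Activ is not collected, and no later analysis plan can restore it.

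**Working it through.** **1. What could "excluded" mean?** The possible readings, set against the other sections:

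| Reading | Consistent with the other sections? |
|---|---|
| Excluded from therapy only | Fits *Withdrawal from randomised therapy* for the intervention arm. Has no meaning for controls, who have no trial therapy to stop, yet the sentence names their period too. |
| Excluded from follow-up | Conflicts with intention to treat. Only withdrawal of consent is said to end data collection. |
| Excluded from the analysis | Conflicts directly with intention to treat. |

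No reading covers both arms and also agrees with the rest of the document.

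**2. The plan's benchmark.** *Sample size calculation* gives a difference of 1.4, SD 3.5, 80% power and 5% significance (two-sided assumed). Per arm, n = 2 × (1.960 + 0.842)² × (3.5/1.4)² = 2 × 7.85 × 6.25 ≈ 98.1, so 99; with the t distribution 99.1, so 100, as stated. Then 200 × 1.035 = 207 (stated 208), and 207/0.70 ≈ 296. The plan's figures reproduce, and the point does not depend on them.

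**3. Illustrative shift.** The document gives no rate of dose increase, no proportion of users and no outcome difference, so every input here is assumed. Let p be the proportion excluded in an arm and d the amount by which their mean DM1-Activ falls below that of the rest (higher taken as better). The retained mean equals the full-arm mean plus p × d, so:

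shift in (intervention − control) = (p_int − p_ctrl) × d

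Take p_ctrl = 5% or 10%, p_int = 2% or 4%, and d = 1.75 or 3.5 points (0.5 or 1 SD):

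| p_int | p_ctrl | d = 1.75 | d = 3.5 |
|---|---|---|---|
| 4% | 5% | −0.0175 | −0.035 |
| 2% | 5% | −0.0525 | −0.105 |
| 4% | 10% | −0.105 | −0.21 |
| 2% | 10% | −0.14 | −0.28 |

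The range is 0.0175/1.4 = 1.25% to 0.28/1.4 = 20% of the target. With p_int = p_ctrl the shift is 0. With the arms swapped the same values carry a plus sign.

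**4. Cross-check by simulation.** With SD 3.5 and an assumed correlation of 0.3-0.5 between outcome and the tendency to a dose rise, excluding 10% of controls and 5% of intervention participants shifts the difference by −0.09 to −0.15. Excluding 5% of each gives about 0.

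**5. Consequence for power, if the shift runs against the intervention.** The effective n per arm is 104/1.035 = 100.5, so SE = 3.5 × √(2/100.5) = 0.494.

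- No shift: Φ(1.4/0.494 − 1.96) ≈ 81%.
- Shift −0.0175: Φ(1.3825/0.494 − 1.96) ≈ 80%.
- Shift −0.28: Φ(1.12/0.494 − 1.96) ≈ 62%.

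**The case against.** The strongest defence is that the document never says these participants leave the analysis. *Withdrawal from randomised therapy* shows that the authors meant to keep people in the primary analysis, and the stray sentence may mean no more than stopping therapy. This stands in part. A reader might infer that the plan has settled on dropping these participants from the primary analysis; the text does not support that, because exclusion is left undefined. Nor is the retention rule breached in terms, since it covers only those withdrawn from the randomised intervention. The broader conflict is with the intention-to-treat commitment. The benign reading still gives controls no coherent status.

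A reader might also infer that the rule biases the trial against the intervention, because controls who fare worse would be removed more often. The document supports neither that frequency nor that direction. It gives an indication for Modafinil only, not for Ritalin. The link to DM1-Activ is indirect. A dose rise might improve later function, and study contact might prompt more dose reviews in the intervention arm.

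The assumed rates also apply to whole arms, whereas a dose can rise mainly in those already taking the drug. If few participants are users, even the lower rates may be too high. The formula further treats all of an excluded participant's data as lost. The primary model is a repeated-measures mixed model that uses available data, so retained month-5 values would probably reduce the shift. However, the document does not say that they are kept for this group, and *Missing data* accepts that missing at random cannot be tested.

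Finally, it is tempting to add these exclusions to the 30% drop-out allowance. *Sample size calculation* does not say whether they fall inside or outside it, so that is not claimed here.

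**Conclusion.** The point holds as an unreconciled and ambiguous post-randomisation rule. That the sentence acts after allocation, in both arms, up to the primary endpoint is plain from the text. Followed as exclusion from follow-up or analysis, it conflicts with intention to treat and could remove participants for a reason related to sleepiness and fatigue.

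That this could bias the comparison is a reasoned possibility. The size and direction cannot be derived from the document. The 0.02-0.28 point range (1-20% of 1.4) is only an illustration resting on the assumed rates and outcome difference. The case for acting now rests on the wording conflict and on the fact that uncollected month-10 data cannot be recovered, not on that range.

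**What to change.** Reconcile *Exclusion criteria* with *Withdrawal from randomised therapy* and *Proposed analysis* on follow-up and analysis status:

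- Confine the drug-stability criterion to eligibility before randomisation.
- State that a participant in either arm whose Modafinil or Ritalin dose changes later stays in follow-up and in the primary intention-to-treat analysis.
- Record the change as concomitant medication, which the outcome schedule in the Appendix already collects at every visit.
- If wanted, examine dose changes in a labelled sensitivity analysis, with details left to the statistical analysis plan.

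The cost is a protocol wording amendment and a note to sites; beyond completing the visits already scheduled, no new data are needed. This concerns follow-up and analysis only. No view is taken on how the drugs should be dosed or on clinical management after a dose change.

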#### Participant selection and enrolment

##### Identifying participants

The study will be conducted on an outpatient basis. The primary route of participant recruitment will be through their neurologist at myotonic dystrophy clinics and neuromuscular centres in the UK, the Netherlands, Germany and France. At each centre, the PI and neurological physicians will be assisted by the study research nurses who will identify potential participants by assessing inclusion and exclusion criteria.

Additionally, participants will also be recruited from the local or national registries of individuals with DM1. Currently, the registries for France, Germany, the Netherlands and the UK contain 1,500, 500, 400 and 300 registered individuals, respectively. Registries contain patients who have specifically shown interest in participating in research and previously consented to be contacted about research in which they can take part. Registries will contact all potentially eligible participants providing a Patient Information Sheet (PIS) and local contact details as well as contacting medical professionals who have shown an interest in the condition to increase awareness beyond the trial sites.

As DM1 is a genetic condition, it is likely that some members of the same family will wish to participate in the study. Immediate family members (mother, father, children, and siblings) may request to attend together for screening and subsequent study visits or separately at a later date. There is no time limit on when a subsequent family member can attend for screening. To avoid treatment contamination, immediate family members will be allocated to the same group, with the first family member being randomly allocated and subsequent member(s) being assigned to the same group as the first. The web-based Tayside Randomisation SysTem (TRuST) will assign the initial family member as per stratification and minimisation criteria (see *Randomisation*), with subsequent family member(s) being assigned by TRuST into the same group. All participants will be asked for consent to allow the study team to enquire if another member of their immediate family is enrolled into OPTIMISTIC. Their name will be required to review the randomisation log to establish their study ID. The study ID of the initial family member will be entered into TRuST, thereby allowing same group allocation.

It may be the case that the carer looks after more than one member of the family wishing to take part. They will be given the opportunity to participate for all family members. However, the carer can opt to not participate at all or to take part for one or all of the family members, whatever is convenient for them.

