### Randomisation

Randomisation will be via a centrally controlled web-based, GCP-compliant randomisation system, run by Tayside Clinical Trials Unit (TCTU) called TRuST (Tayside Randomisation SysTem).

Randomisation will occur as indicated below:It will be stratified by site.It will be minimised for baseline DM1 severity measured by the Muscular Impairment Rate Scale (MIRS) 5-point scale.It will be minimised for baseline involvement (or not) of a caregiver.

For immediate family member participation TRuST will assign the initial family member as per stratification and minimisation criteria (see *Randomisation*), with subsequent family member(s) being assigned by TRuST into the same group. All participants will be asked for consent to allow the study team to enquire if another member of their immediate family is enrolled into OPTIMISTIC. Their name will be required to review the randomisation log to establish their study ID. The study ID of the initial family member will be entered into TRuST thereby allowing same group allocation.

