### Statistics and data analysis

#### Sample size calculation

The primary outcome is the DM1-Activ scale, which is a Rasch-built measure of activity and participation for patients with DM1 and is currently the best such measure for these patients. Based on a minimum clinically important mean difference of 1.4 on the 40-item DM1-Activ scale, standard deviation of 3.5 and effect size = 0.4, 80 % power and 5 % significance level, we need a sample size of 100 in each arm, or 200 in total.

DM1 is a genetic condition so it is likely that some members of the same family will take part in the study. To avoid the risk of contamination, immediate family members (mother, father, children, and siblings) will be allocated to the same group, with the first family member being randomly allocated and subsequent members being assigned to the same group as the first. This means that there will be some clusters of more than one individual and the sample size needs to be inflated to account for this. Newcastle estimates that this may affect 50 % of their participants, the other sites estimate that fewer than 10 % of participants will be part of a family group. All sites estimate that almost all family groups will comprise two individuals. Using estimates of distributions of recruitment across sites (Newcastle = 23 %; Nijmegen = 30 %; Paris = 33 %; and Munich = 13 %) and the above family group proportions gives an average cluster size of 1.17. Using a conservative intra-cluster correlation coefficient of 0.20, gives an inflation factor of 1.035, meaning the recruitment target needs to be increased by 10 to 296. After allowing for up to 30 % drop-out this gives a final sample size of 208, or 104 participants per arm.

These are conservative estimates (especially the minimum clinically important difference). The clinical OPTIMISTIC sites between them see well over 1,000 DM1 patients per year, which gives OPTIMISTIC a good pool of potentially eligible participants. Around 70 % of DM1 patients are expected to be eligible for OPTIMISTIC.

We will be using one of our secondary outcomes, the 6-minute walk test (6MWT) as an additional validation of the DM1-Activ scale, meaning that we have also powered this secondary outcome. The DM1-Activ sample size of 208 gives over 90 % power for the 6MWT based on a mean difference of 40 m, standard deviation of 80 m and a baseline of 450 m.

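### Relatives who join after the first family member's allocation can enter knowing their arm, so concealment may be lost for up to about one participant in ten

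*Protocol article*

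**What the plan says.** The section Identifying participants sets the allocation rule for immediate relatives: "with the first family member being randomly allocated and subsequent member(s) being assigned to the same group as the first". The stated reason is to avoid contamination between arms. Relatives "may request to attend together for screening and subsequent study visits or separately at a later date", and for those who come later: "There is no time limit on when a subsequent family member can attend for screening". The assignment is made by linking IDs: "The study ID of the initial family member will be entered into TRuST, thereby allowing same group allocation". The Randomisation section repeats the rule, and Intervention allocation names families as the exception to 1:1 allocation.

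Three other statements bear on this:

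- **Blinding (Study description, text after Fig. 2):** "Participants will not be blind to allocation, but the study outcome measures listed in the Appendix will be collected by staff who are blind to" (the quote stops one word short; what these staff do not know is the arm).
- **Eligibility (Inclusion criteria):** "Judgements as to whether a potential participant meets an inclusion criterion are made by the treating clinician unless stated otherwise". The Exclusion criteria give the same role to the treating clinician, and whether depression is severe is left to clinical judgement.
- **Extent (Sample size calculation):** on family groups, "Newcastle estimates that this may affect 50 % of their participants". The other sites expect a share below 10%, and nearly all groups are expected to be pairs.

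**The concern.** Central web randomisation conceals an allocation only while it is still undetermined. Once the first member has been allocated, the arm of every later relative is fixed, and an unblinded patient can tell the family what it is. The relative can then decide whether to come forward with the arm known. The treating clinician can judge eligibility knowing it too, because nothing in the text keeps the family's allocation from that clinician. The fatigue threshold for entry and the baseline questionnaires rest on self-report, given with help from the nurse and caregivers (Data collection), and one carer may take part for several relatives.

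What is on offer differs by arm. The intervention brings 10 to 14 therapy sessions and possibly a gym membership. The comparison is usual care, which at minimum is roughly a yearly visit with an ECG. Later relatives could therefore differ between arms in number and in kind. This is the recruitment bias familiar from cluster trials in which individuals are enrolled after the cluster is allocated. Blinded outcome collection does not address it, because the selection happens at entry.

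**Working it through.** **Reproducing the plan's own figures (Sample size calculation).**

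- Difference 1.4, SD 3.5, 80% power, 5% two-sided (two-sided assumed): the normal approximation gives 99 per arm; the plan states 100, or 200 in total.
- Dropout of 30%: 200 / 0.7 = 285.7, so 286.
- Family inflation: 1 + (1.17 − 1) × 0.20 = 1.034; the plan states 1.035. Then 286 × 1.035 = 296.
- Completers: 148 × 0.7 = 103.6 per arm, rounded to 104, or 208 in total.

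**Share of participants who are second family members.** The inputs are recruitment shares of 23% (Newcastle), 30%, 33% and 13% (these sum to 99%), family shares of 50% at Newcastle and below 10% elsewhere, and groups of two.

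- Ceiling, with exactly 10% elsewhere: 0.23 × 0.50 + (0.30 + 0.33 + 0.13) × 0.10 = 0.115 + 0.076 = 0.191 of participants in pairs. Half are second members: 0.191 / 2 = 0.0955, and 0.0955 × 296 = 28.3.
- Floor, with no families elsewhere: 0.115 / 2 = 0.0575, and 0.0575 × 296 = 17.0.
- Newcastle alone: 0.23 × 296 = 68; half of 50% is 25%, or 17 people.

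**Check against the stated average cluster size of 1.17.**

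- Read as 1 plus the share of participants in pairs, it gives 0.17 in pairs, so 0.085 × 296 = 25 second members. This implies (0.17 − 0.115) / 0.76 = 7% in families at the other sites, which agrees with their stated limit.
- Read as participants per family unit, it gives 1 − 1/1.17 = 14.5%, or 43 second members. This needs 29% in pairs overall and (0.29 − 0.115) / 0.76 = 23% at the other sites, which contradicts that limit. I therefore do not use it.

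**From second members to unconcealed entrants.** A second member loses concealment only if he or she enters after the first member's allocation. If a fraction j of pairs is fully enrolled before allocation, the unconcealed share is at most 0.0955 × (1 − j). The document does not give j. Across its possible range:

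| j (assumed) | Share | Of 296 |
|---|---|---|
| 0 | 9.6% | 28 |
| 0.5 | 4.8% | 14 |
| 1 | 0% | 0 |

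**Unequal joining, by assumption only.** With 28 later members and the other 268 split evenly (134 per arm), a 1:1 split of the 28 gives 148 and 148, 2:1 gives about 153 and 143, and 3:1 gives 155 and 141. The document gives no basis for choosing among these.

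**The case against.** The same-arm rule is a deliberate and disclosed trade-off. Its purpose is stated, its clustering is counted in the sample size, and the departure from 1:1 is declared. Relatives may attend together, and the section Consenting participants already has immediate family members invited with the patient's permission. The main entry criteria (a genetic test, a fatigue cut-off, independent walking) limit discretion. Much of this stands, and it is why the rule itself is not criticised. But the invitation does not require relatives to be enrolled before the first member is randomised, and nothing in the anti-contamination aim calls for open-ended entry afterwards.

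A reader might infer more than the text supports:

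- **That one in ten will in fact enter unconcealed.** That figure takes 10% where the other sites say less, and treats every second member as a late joiner. It is a ceiling.
- **That the treatment effect is biased by a stated amount.** This needs the share of late joiners in each arm and how far they differ from other participants. The document gives neither. The planned outcome is also change in DM1-Activ, in a model with severity, caregiver involvement and site, so a difference in level would largely cancel. Only a difference in change would carry through in full.
- **That looking up relatives unblinds outcome staff.** The text says only "Their name will be required to review the randomisation log to establish their study ID". It does not say that the log displays allocation or that outcome assessors read it.
- **That the lack of a sensitivity analysis is itself a defect.** That may sit in the statistical analysis plan, which is not shown. No analysis, however, restores concealment, and one can separate these participants only if the order of enrolment relative to the family's allocation is recorded.

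**Conclusion.** The concern holds as a weakness of the enrolment rule. Relatives screened after the first member's allocation can enter with their arm known to them and to the clinician who judges eligibility, and recruitment of such relatives can differ by arm. On the site estimates this affects at most about one participant in ten: up to about 28 of 296, about 17 if only Newcastle has families, and fewer to the extent that pairs are enrolled together before allocation. These counts assume family groups of two and the planned recruitment shares. Differential recruitment is something the design permits; the document does not show that it will happen, and the bias cannot be quantified from it.

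**What to change.** Keep the same-arm rule and change the order of steps.

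1. When the index patient consents, ask which immediate relatives are willing to take part. Where feasible, complete their consent, eligibility and baseline before the family is randomised as one unit.
2. Let relatives who appear later still join the family's arm, but record for each participant whether enrolment came after the family's allocation, and report these numbers by arm.
3. Pre-specify a sensitivity analysis of the primary outcome limited to participants enrolled before their family's allocation.

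The cost is a short wait for some index patients, one flag variable and one analysis with up to about 10% fewer participants. At that ceiling its standard error would be about 5% larger (1 / √0.9045 = 1.05, ignoring clustering). Nobody is excluded and the protection against contamination is unchanged.
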